#### Power analysis

Power analysis for aim 1 is based on main effect differences at the end of the intervention. We estimated the per cell sample size assuming a moderate effect size (Cohen’s *d* = 0.5), alpha = 0.05, and power = 0.80 using the fpower SAS macro available at http://www.datavis.ca/sasmac/fpower.html. Based on combined data from our pilot study measures, the minimum detectable difference (MDD) for the treatment main effects will be clinically meaningful. For example, we will be able to detect a 2.3-point difference in insomnia severity between those receiving COPD-ED versus those not, averaged across the other treatment conditions. The MDD for other outcomes includes Actiwatch® sleep efficiency = 6.72, CRQ-F = 0.51, and the Profile of Moods States Fatigue subscale (POMS-F) = 2.76. Between-group effect size estimates from our pilot study ranged from 0.35 for sleep efficiency to 1.03 for insomnia severity, comparing the proposed treatment components. Path models using 7–14 parameters can be estimated according to the sample size convention of 10 to 20 cases per parameter [61], thus, our simple path models can be estimated. We further conservatively estimate an attrition rate of 15 % by the end of the study. Therefore, we will enroll a total of 166 and retain 140 (35 per group) subjects in the proposed study.

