## Methods: assignment of interventions

A randomization schedule was developed using Excel whereby the four treatment groups were randomly ordered in blocks of four and sequentially assigned through REDCap according to stratum. We have four strata defined by sex and COPD severity (two levels); this process is managed separately by site. The complexity of the design (four treatment arms × four strata × two sites) is assumed to reduce predictability for the sequence of group assignment for any given participant. Non-blinded study staff generate allocation by REDCap and assign participants to interventions. Personnel administering and scoring the PFTs, actigraphy and posttest/follow-up sleep diaries are blinded to group assignment.

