### Statistical analysis

#### Test of specific hypotheses

Descriptive statistics (means, standard deviation, frequency) and plots are used to screen the data prior to our main analyses. Necessary transformation and imputations are conducted based on the raw data distribution. Baseline adjustment for covariates (e.g., age, COPD severity (PFT), and gender) will be incorporated into the main effect analyses to reduce error variance and improve statistical power [69]. Data analyses is performed using SAS 9.3 statistical software (SAS Inc., Cary, NC, USA) and Mplus 6.0 (Muthén & Muthén, Los Angeles, CA, USA). All tests will be two-sided and an error rate of *α* <0.05 will be considered statistically significant. The test of each specific aim is described below, and all statistical analysis will employ an intent-to-treat approach. A fully specified statistical analysis plan will be written before unmasking.

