Aim 1: to determine the efficacy of individual treatment components, CBT-I and COPD-ED, on insomnia and fatigue. In this 2 × 2 design, participants are randomized into four groups created by crossing the two factors, CBT-I versus AC1 and COPD-ED versus AC2 (see Table 3). We hypothesize that both components will improve insomnia and decrease fatigue following the six-session program, and that participants will maintain these gains at 3 months post intervention. Our factorial design permits the test of an interaction between the two treatment components, and we will assess for the presence of a strong interaction effect. However, we do not anticipate a strong synergy of the treatments since our pilot work showed that both had within-group improvement, and the hypothesized mechanisms for change differ. If the interaction is negligible, we will proceed with the interpretation of averaged main effects as shown in Table 3. The statistical tests for both components will be more robust than tests against a simple control condition because they are averaged across the levels of the other treatment. That is, the effect of each component will be tested controlling for the effect of the other. This is an efficient design because all subjects will be used to test both components. Finally, it may be more acceptable to participants since all receive supportive contact and only one out of four conditions does not receive a component hypothesized as an active treatment for insomnia in COPD patients. We will employ mixed-effects models using insomnia and fatigue as time-varying dependent variables and treatment groups as fixed effects. Demographic and clinical characteristics will be entered as time-invariant covariates if baseline group differences are observed despite randomization. Individuals’ baseline sleep measures and change over time (i.e., intercept and slope) will be modeled as random effects. The null hypothesis will be rejected if a significant treatment × time interaction is observed. For example, a significant CBT-I × time effect in the hypothesized direction would mean that participants receiving CBT-I improved more than those who did not, averaged across the other conditions. The mixed models will be run using PROC MIXED SAS 9.3 (SAS Inc., Cary, NC, USA) and estimated by residual maximum likelihood (REML). Covariance pattern structures (compound symmetry and unstructured) will also be examined, and models will be compared using likelihood ratio tests or Akaike’s Information Criteria (AIC) which is a function of the log likelihood and can be compared across models.

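### The Aim 1 model has two conflicting covariate rules, and the one triggered by baseline imbalance would almost never select the factors that stratify randomisation

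*Protocol article*

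**What the plan says.** Three places in the protocol article bear on the point.

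- Test of specific hypotheses, opening paragraph: "Baseline adjustment for covariates (e.g., age, COPD severity (PFT), and gender) will be incorporated into the main effect analyses to reduce error variance". Better power is the other stated purpose. No condition is attached, and the list is given as examples.
- Test of specific hypotheses, Aim 1: "We will employ mixed-effects models using insomnia and fatigue as time-varying dependent variables and treatment groups as fixed effects". The covariate rule follows: "Demographic and clinical characteristics will be entered as time-invariant covariates if baseline group differences are observed despite randomization". The null hypothesis is rejected on a significant treatment × time interaction. Each person's baseline level and change over time are random effects. Trial design gives three measurements of the outcomes: T1 (baseline), T2 (end of intervention) and T3 (3 months).
- Methods: assignment of interventions: "the four treatment groups were randomly ordered in blocks of four and sequentially assigned through REDCap according to stratum". It continues: "We have four strata defined by sex and COPD severity (two levels); this process is managed separately by site". There are two sites.

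Neither covariate sentence names site.

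**The concern.** Age, gender and COPD severity are demographic and clinical characteristics, so both rules govern them. One rule always includes them, to gain precision. The other includes them only after an imbalance has been seen. The article does not say which prevails.

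The conditional rule is also poor in itself. After sound randomisation an observed baseline difference is chance. It does not show whether the variable predicts the outcome, which is what decides whether adjustment helps. No variable list or threshold is given, so the form of the Aim 1 model would depend on the draw of the randomisation. The rule also works against the design: factors that stratified blocks hold in balance are the ones least likely to be selected, although they are natural candidates for adjustment.

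At stake are precision and a model known in advance.

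**Working it through.** **1. The plan's own figure.** Power analysis uses d = 0.5, alpha = 0.05 and power 0.80; tests are two-sided. By the normal approximation, n per factor level = 2 × (1.96 + 0.8416)² / 0.5² = 62.8, so 63, or 32 per cell. The planned 35 per cell (70 per level) gives Φ(0.5 × √(70/2) − 1.96) = Φ(0.998) = 0.84. For attrition, 140 / 0.85 = 164.7, so 165 against the stated 166. The sample size is sound and is not in question.

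**2. What an imbalance rule would select.** Sex (2) × severity (2) × site (2) makes eight allocation cells. With blocks of four over four arms, arm counts within a cell differ by at most 1. Each level of sex spans four cells, so two arms of about 35 can differ by at most 4 people on it. The same holds for severity level and for site.

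A simulation used N = 140, blocks of four within the eight cells, and 8 scenarios of 6,000 runs. Its assumptions, not in the article, were an imbalance threshold of p < 0.05 across the four arms and prevalences of 35% (one site), 45% (one sex) and 50% (one severity level). Sex, severity and site were selected in none of the 48,000 runs. Age, which is not stratified, was selected in about 5%.

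For k independent, unstratified variables screened at 5%, the chance of at least one trigger is 1 − 0.95^k: 0.23 for k = 5 and 0.40 for k = 10. Both k and the threshold are assumptions.

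**3. What this does to the term that is tested.** Write the outcome of person i in group g at visit t as μ_gt + γx_i + b_i + e_it. Then the change from T1 to T2 is (μ_g2 − μ_g1) + (e_i2 − e_i1): a time-constant covariate effect γx_i drops out.

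A refit with three visits, a random intercept, N = 140 and assumed covariate R² of 0.1 to 0.3 agrees. Adding sex, severity and site left the CBT-I × time standard error unchanged with complete data (ratio 1.0000) and changed it by 0.2% to 0.9% with 15% random dropout. The unadjusted T2 − T1 contrast had type I error 0.050, 0.049 and 0.052.

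So covariates entered only as main effects do little for the Aim 1 test under either rule. They help if they predict change, which needs covariate × time terms.

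**4. What is recoverable.**

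*Stratification factors that predict change.* At a baseline–outcome correlation of 0.5, the SD of change equals the SD of the outcome, since √(2(1 − 0.5)) = 1, so d stays 0.5. If the factors explain a share R² of the change variance, power is Φ(0.5/√(1 − R²) × √35 − 1.96): 0.84, 0.88, 0.91 and 0.94 for R² = 0, 0.1, 0.2 and 0.3. That is up to about 10 points. A simulation with a weaker link (change-related variance 0.10 of the residual outcome variance) gave only 0.84 against 0.85.

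*The role of the baseline outcome.* With T1 as a response and group means free at T1, the T2 − T1 contrast behaves like a change score, with effect d/√(2(1 − ρ)). With T1 as a covariate the effect is d/√(1 − ρ²). With d = 0.5 and 70 per level:

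| Assumed ρ | T1 as free response | T1 as covariate |
|---|---|---|
| 0.3 | 0.71 | 0.87 |
| 0.5 | 0.84 | 0.93 |
| 0.7 | 0.97 | 0.985 |

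**The case against.** The strongest reply is that the two sentences can be reconciled: a core set of precision covariates always enters, and further characteristics enter if imbalanced. On that reading sex and severity are never dropped. But the conditional sentence is not limited to further characteristics, and nothing in the article ranks the two rules. Even so read, the extra covariates would still be chosen by chance imbalance.

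Several other replies stand, at least in part:

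- **Size of the loss.** A reader might apply the usual formulas for omitted stratification factors: interval inflation 1/√(1 − R²) − 1 = 5.4% or 11.8%, and true test level 0.039 or 0.028, at R² = 0.10 or 0.20. These describe a comparison of post-treatment values alone. The article tests treatment × time, where step 3 shows almost none of this.
- **Site.** A reader might call its absence an error. The covariate list is open and a full analysis plan is promised before unmasking, so site only supports the point.
- **A fixed set.** The opening paragraph does not promise one. It promises adjustment without a condition.
- **Analyst discretion.** Data collection says analysis staff are blinded to group, and the analysis plan precedes unmasking. Steering towards a favourable result is therefore not a fair charge. Dependence on chance imbalance remains.

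The unseen analysis plan does not remove the main point. This is a stated rule that conflicts with another stated rule, and that plan would have to depart from one of them.

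**Conclusion.** The point holds as a contradiction between two published covariate rules, one of which is data-dependent and ill-suited to a stratified, blocked design. The harm is lost precision and a model not known in advance. A reader might infer bias or an inflated type I error; neither is shown.

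The contradiction rests on the text alone. The size rests on assumptions the article does not supply: the imbalance threshold, the share of change explained by the stratification factors, and the baseline–outcome correlation. Over the values tried, prespecified factors acting on change add about 1 to 10 points of power, and nothing if they do not predict change. Moving the baseline outcome from free response to covariate adds 16 points at ρ = 0.3, 9 at 0.5 and 1 to 2 at 0.7. The latter comparison takes the Aim 1 model to leave group means free at T1, which is the natural reading but is not stated.

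The balance argument covers the two-level severity stratum. A continuous lung-function value is balanced only in part.

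**What to change.** - Delete the conditional sentence in the Aim 1 paragraph.
- Name one covariate set for every Aim 1 model, whatever the observed imbalance: sex, COPD-severity stratum, site and age. If T1 stays in the response, add their interactions with time so that they act on the tested contrast.
- Use the baseline outcome in one role only: either as a covariate with T2 and T3 as responses, or as a response with group means constrained equal at T1. It cannot be both. With the covariate option, restate the rejection rule as the treatment effect at the named visit, because treatment × time over T2 and T3 alone would test only whether the effect changes between them.
- Describe baseline imbalance in the report, but do not let it select the model.

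The cost is wording and a few degrees of freedom: four parameters for the covariates, or 4 + 4 × 2 = 12 with visit interactions over three visits. All these variables are already collected, and the sample size need not change.

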Results from previous studies of predictors of positive outcomes of CBT-I suggest that mechanisms include changes in sleep-related beliefs, sleep habits, emotional arousal and self-efficacy for sleep [23]. Thus, our contribution here is expected to be knowledge of the efficacy and mechanisms of the components of a novel insomnia therapy for people with COPD and a detailed understanding of which patients are most likely to benefit from the therapy. This contribution will be significant because it is a necessary step in the development of effective non-pharmacological therapies for insomnia coexisting with COPD. Once such advances in therapy for insomnia coexisting with COPD become available, results can be used to further develop and make available effective and efficient insomnia therapies for people with COPD. Components of therapy found to be most important for positive outcomes can be included in new, more efficient therapies. It is expected that what we learn will be equally applicable to the prevention of insomnia and fatigue in people with COPD, potentially leading to them having longer, higher-quality and more productive lives and to society having to burden lower costs related to insomnia in COPD.

We are testing components of a novel therapy (CBT-I and COPD-ED) in an understudied population using a highly efficient study design. Despite the established need for such a therapy for people with COPD, this group is understudied, perhaps because of challenges such as recruiting subjects with COPD and managing periodic exacerbations of COPD that could occur during treatment. Furthermore, people with insomnia coexisting with COPD are subject to exacerbations of their illness that predispose them to recurrent insomnia and may interfere with CBT-I outcomes. The research represents a new and substantive departure from the usual insomnia therapy, specifically by combining traditional CBT-I with disease-specific education (COPD-ED) to enhance self-efficacy for the management of COPD. Enhancing self-efficacy for COPD is likely to reduce insomnia and fatigue by attenuating the anxiety and depressed mood associated with the disease.

### Aim 1

To determine the efficacy of individual treatment components, CBT-I and COPD-ED, on insomnia and fatigue. Our hypothesis is that both components will decrease insomnia and fatigue at the end of the six-session treatment period, and that these differential effects will be sustained for at least 3 months post treatment.

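### Aim 1 is powered on each component's difference at the end of the intervention but decided by a treatment × time interaction over three visits, so the powered quantity is not the tested one

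*Protocol article*

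**What the plan says.** Aim 1 (protocol article, Background) has two parts. The first is that "both components will decrease insomnia and fatigue at the end of the six-session treatment period". The second is that these effects last at least 3 months after treatment. Trial design places the outcome measurements at baseline (T1), immediately after the intervention (T2) and 3 months later (T3).

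The Power analysis section addresses the first part only: "Power analysis for aim 1 is based on main effect differences at the end of the intervention". It assumes d = 0.5 with "alpha = 0.05, and power = 0.80 using the fpower SAS macro", and concludes that "we will enroll a total of 166 and retain 140 (35 per group) subjects in the proposed study". Table 3 shows that each main effect compares 70 with 70.

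The Aim 1 text under Test of specific hypotheses describes mixed-effects models in which individuals' baseline measures and "change over time (i.e., intercept and slope) will be modeled as random effects". The decision rule follows: "The null hypothesis will be rejected if a significant treatment × time interaction is observed". A CBT-I × time effect is given as the example. The article does not say whether the fixed effect of time is linear or categorical. Compound symmetry and unstructured covariance are also to be examined and compared by fit. A fully specified analysis plan is promised before unmasking.

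**The concern.** The hypothesis describes a step (improvement by T2) followed by a plateau (maintenance to T3), and the sample size rests on the step. The stated rule tests neither a T2 nor a T3 contrast. It tests whether the profiles over three visits differ, and what that means depends on how time enters the model.

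With linear time the tested quantity is a slope, which gives the powered time point little or no weight. With categorical time it is a joint test of T2 and T3 that does not separate the two parts of Aim 1. On either reading the stated power does not belong to the test that decides efficacy, and the end-of-treatment claim has no test of its own. Some fading is conceivable on the article's own account, since the Background says exacerbations predispose these patients to recurrent insomnia.

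**Working it through.** **Inputs from the article.** d = 0.5, two-sided alpha 0.05, 70 v 70 per main effect, outcomes at T1, T2 and T3.

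**Assumptions (not in the article).** SD 1 at each visit; compound symmetry with correlation ρ = 0.3, 0.5 or 0.7; complete data on 140; time coded 0, 1, 2 (visits), or in weeks as 0, 6, 19 or 0, 7, 20.

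**1. The article's own figure.** For d = 0.5, two-sided 0.05 and 80% power, the t test needs 64 per factor level, which is 32 per cell or 128 in all (power 80.1%). At 70 per level power is 83.6%. For attrition, 140/0.85 = 164.7, in line with 166. The stated size is slightly generous for an unadjusted T2 difference.

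**2. Weights under linear time.** With balanced complete data the fixed slope difference is Σ(w × effect)/Σw², where w = t − mean(t).
- Visits 0, 1, 2: w = −1, 0, +1; Σw² = 2. T2 has zero weight and the test is T3 minus T1.
- Weeks 0, 6, 19: w = −8.33, −2.33, +10.67; Σw² = 188.67.
- Weeks 0, 7, 20: w = −9, −2, +11; Σw² = 206.

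In weeks, a benefit at T2 counts slightly against the component.

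**3. Power of the slope test.** SE = √(2(1 − ρ)/(70 Σw²)). Example with weeks 0, 7, 20 and ρ = 0.5: SE = √(1/(70 × 206)) = 0.00833.
- Held (0, 0.5, 0.5): slope (−1 + 5.5)/206 = 0.0218; z = 2.62; power 0.75.
- Half faded (0, 0.5, 0.25): slope (−1 + 2.75)/206 = 0.0085; z = 1.02; power 0.17.
- Fully faded (0, 0.5, 0): slope −1/206 = −0.0049; z = −0.58, the wrong sign.

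Power at ρ = 0.3 / 0.5 / 0.7:

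| Test | Held | Half faded | Fully faded |
|---|---|---|---|
| Slope, visits 0, 1, 2 | 0.71 / 0.84 / 0.97 | 0.24 / 0.32 / 0.48 | 0.05 at each ρ, half in each direction |
| Slope, weeks 0, 6, 19 | 0.57 / 0.72 / 0.91 | 0.12 / 0.15 / 0.22 | 0.09 / 0.11 / 0.15, almost all in the wrong direction |
| Slope, weeks 0, 7, 20 | 0.60 / 0.75 / 0.92 | 0.14 / 0.17 / 0.26 | wrong sign (z = −0.58 at ρ = 0.5) |

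A rough REML mixed-model simulation (100 runs per scenario, with convergence warnings) agreed for the full fade: 2% rejections with 0, 1, 2 and 14% with 0, 6, 19, of which 1% in each case was in the right direction.

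**4. T2 contrast, whatever happens at T3.**
- Change from baseline: standardised effect 0.5/√(2(1 − ρ)); z = 2.50 / 2.96 / 3.82; power 0.71 / 0.84 / 0.97.
- Baseline as covariate: 0.5/√(1 − ρ²); z = 3.10 / 3.42 / 4.14; power 0.87 / 0.93 / 0.99.

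**5. Joint 2-df test with categorical time.** For effects e2 at T2 and e3 at T3, the noncentrality under compound symmetry is [70/(2(1 − ρ))] × [e2² + e3² − (e2 + e3)²/3].
- Held: bracket 0.5 − 1/3 = 0.167.
- T2 only, or T3 only: 0.25 − 0.25/3 = 0.167, the same value.

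Noncentrality is 8.33 / 11.67 / 19.44 and power 0.74 / 0.87 / 0.98 for all three patterns. Half faded gives 0.3125 − 0.1875 = 0.125, noncentrality 6.25 / 8.75 / 14.58 and power 0.60 / 0.76 / 0.94.

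**The case against.** A reader might infer that a component which works and then fades will be missed. The article does not support that as a flat statement, for two reasons. First, the low power depends on linear fixed time, which is not stated. The slope is mentioned as a random effect, whereas the tested term is a fixed interaction, and the covariance patterns also listed are compatible with categorical visits. With categorical time a fully faded effect is detected with 0.74 to 0.98 power. Second, sustained benefit is half of the hypothesis, so a fading component would fail that half under any analysis. What is lost is a separate verdict on the end-of-treatment half.

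Other points on that side also stand:
- With visits coded 0, 1, 2, a fully held effect has the same power as an unadjusted T2 change contrast.
- Part of the gap between the slope test and the baseline-adjusted T2 contrast is the gain from covariate adjustment, not a fault of the interaction rule.
- Compound symmetry leaves out the slope variance that the planned model allows for. The equality of the three 2-df patterns also depends on it: under AR(1) with correlation 0.3, power is 0.78 for T2 only and 0.66 for the other two.
- Choosing a covariance structure by fit is common practice, and no harm from it has been quantified here.

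It can also be said that time coding and follow-up contrasts belong in the later analysis plan. That would answer an omission. It does not answer a rejection rule that the article already states and that differs from the quantity it powered.

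**Conclusion.** The mismatch is real under either reading of time: the sample size is justified by a T2 main-effect difference, and the null is rejected on a treatment × time interaction with no T2 contrast named.

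- **Linear time.** T2 carries zero or slightly negative weight. An effect that half fades has about 0.12 to 0.48 power, and one that fully fades is detected in the right direction no more often than chance. A held effect has 0.57 to 0.75 in weeks, or 0.71 to 0.84 with 0, 1, 2 coding, at correlations of 0.3 to 0.5.
- **Categorical time.** For a held or fully faded effect the 2-df test has 0.87 to 0.98 power at correlations of 0.5 or more and 0.74 at 0.3. Rejection still leaves open whether the end-of-treatment or the sustained part holds.

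These sizes rest on assumed correlations, time coding, compound symmetry and complete data. The point does not show that the trial is too small: 70 per level exceeds the 64 that the stated inputs require for a T2 difference.

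**What to change.** In the Aim 1 analysis text, and in the analysis plan to be written before unmasking:

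1. Treat time as categorical.
2. Adjust for the baseline value of the outcome, or constrain baseline means to be equal across arms.
3. Replace the treatment × time rejection rule with each component's main-effect contrast at T2, averaged over the other component, as the Aim 1 test.
4. Test the same contrast at T3 separately for maintenance.

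As a secondary suggestion, fix the covariance structure in advance (for example unstructured) instead of choosing it by fit.

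The Power analysis section then refers to the contrast actually tested, and is conservative for it when baseline is adjusted for. The cost is wording and a few more covariance parameters. No participants, visits or measurements are added.
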